## Abstract

**Background:**

Novel coronavirus SARS-CoV-2 is known to be susceptible in vitro to exposure to hydroxychloroquine and its effect has been found to be potentiated by azithromycin. We hypothesise that early administration of hydroxychloroquine alone or in combination with azithromycin can prevent respiratory deterioration in patients admitted to intensive care due to rapidly progressive COVID-19 infection.

**Methods:**

Design: Prospective, multi-centre, double-blind, randomised, controlled trial (RCT). Participants: Adult (> 18 years) within 24 h of admission to the intensive care unit with proven or suspected COVID-19 infection, whether or not mechanically ventilated. Exclusion criteria include duration symptoms of febrile disease for ≥ 1 week, treatment limitations in place or moribund patients, allergy or intolerance of any study treatment, and pregnancy. Interventions: Patients will be randomised in 1:1:1 ratio to receive Hydroxychloroquine 800 mg orally in two doses followed by 400 mg daily in two doses and azithromycin 500 mg orally in one dose followed by 250 mg in one dose for a total of 5 days (HC-A group) or hydroxychloroquine + placebo (HC group) or placebo + placebo (C-group) in addition to the best standard of care, which may evolve during the trial period but will not differ between groups. Primary outcome is the composite percentage of patients alive and not on end-of-life pathway who are free of mechanical ventilation at day 14. Secondary outcomes: The percentage of patients who were prevented from needing intubation until day 14, ICU length of stay, and mortality (in hospital) at day 28 and 90.

**Discussion:**

Although both investigational drugs are often administered off label to patients with severe COVID-19, at present, there is no data from RCTs on their safety and efficacy. In vitro and observational trial suggests their potential to limit viral replication and the damage to lungs as the most common reason for ICU admission. Therefore, patients most likely to benefit from the treatment are those with severe but early disease. This trial is designed and powered to investigate whether the treatment in this cohort of patients leads to improved clinical patient-centred outcomes, such as mechanical ventilation-free survival.

**Trial registration:**

Clinical trials.gov: NCT04339816 (Registered on 9 April 2020, amended on 22 June 2020); Eudra CT number: 2020-001456-18 (Registered on 29 March 2020).

## Administrative information

Note: the numbers in curly brackets in this protocol refer to SPIRIT checklist item numbers. The order of the items has been modified to group similar items (see http://www.equator-network.org/reporting-guidelines/spirit-2013-statement-defining-standard-protocol-items-for-clinical-trials/).

## Introduction

### Background and rationale {6a}

At the beginning of 2020, the novel coronavirus disease (COVID-19) began to spread from Asia to Europe and beyond forcing the World Health Organization to declare a global pandemic. Infected patients shed the virus for a median of 20 days [1]. Up to 10% of COVID-19 infected patients develop a severe form of disease requiring intensive care admission and some of them die. SARS-Cov2 is an encapsulated positive-strand RNA virus that uses ACE-2 of type 2 pneumocytes as binding sites. It has been hypothesised (Gattinoni 2020 ICM editorial) that initial hypoxemia caused by loss of primary injury to pulmonary vasculature leads to hyperventilation and patients self-inflicted lung injury predominantly in lung areas of increase stress and strain. In turn, later during the course of the disease, ARDS develops with a typical restrictive pattern of a stiff, wet and recruitable lung. At present, there is no evidence-based causative treatment of SARS-CoV-2 and there is a burning need of randomised controlled trials to find effective therapeutic strategies intervention.

Chloroquine has been used for malaria treatment and chemoprophylaxis, and hydroxychloroquine is used for the treatment of rheumatoid arthritis, systemic lupus erythematosus and porphyrias. Both drugs have in vitro activity against SARS-CoV, SARS-CoV-2 and other coronaviruses, with hydroxychloroquine having relatively higher potency against SARS-CoV-2 known to be susceptible in vitro to exposure to hydroxychloroquine [2–4]. At the moment, clinical trials are ongoing to test clinical efficacy in pre- and post-exposure prophylaxis in SARS-CoV-2. In one highly cited French non-randomised observational study by Gautret et al., a significant reduction of virus carriage has been observed in patients coincidentally treated by azithromycin in addition to hydroxychloroquine [5] as a part of initial empirical therapy of community-acquired pneumonia. Azithromycin is a macrolide antibiotic, which binds to the 50S subunit of the bacterial ribosome, thus inhibiting translation of mRNA. The positive-sense RNA viruses and indeed all genes defined as positive-sense can be directly accessed by host ribosomes to immediately form proteins and the effects of azithromycin on this process are not known. No data are available at present on the clinical efficacy of hydroxychloroquine alone or in combination with azithromycin, and it is likely that any treatment affecting virus replication would only be effective if administered early, before overt ARDS develops.

In the light of this, we designed a trial in which we test a hypothesis that early administration of hydroxychloroquine alone or in combination with azithromycin can prevent respiratory deterioration in patients admitted to intensive care due to rapidly progressive COVID-19 infection.

## Objectives {7}

The primary study objective is to test the hypothesis that early administration of combination therapy slows disease progression and improves mechanical ventilation-free survival.

The secondary (exploratory) study objective is to investigate whether the intervention decreases the viral load and influences oxygenation and mechanical feature of the lung.

SPIRIT guidance: Specific objectives or hypotheses.

## Trial design {8}

Prospective, randomised (1:1:1), placebo and active-comparator controlled, parallel group, double-blind exploratory trial.

## Methods: participants, interventions and outcomes

### Study setting {9}

This is a multi-centre trial conducted in intensive care units of 8 hospitals (6 university hospitals and 2 district general hospitals) in the Czech Republic. The updated list of centres including contact details of site investigators can be found in the Appendix.

### Eligibility criteria {10}

For participants, the following eligibility criteria were set:

#### Inclusion criteria

Adult (> 18 years)Within 24 h of admission to the intensive care unitProven or suspected COVID-19 infection

#### Exclusion criteria

Symptoms of febrile disease for ≥ 1 week at enrolmentPregnancy or inability/unwillingness to perform pregnancy test at and 28 days after enrolmentTreatment limitations in place or moribund patientsAllergy, intolerance or contraindication to any study drug, such as long QT syndromes, myasthenia gravis, pre-existing maculopathy or retinopathy, allergies or known deficiency of glucose-6-phosphate dehydrogenaseKnown HIV positivitySignificant liver disease such as cirrhosis Child-Pugh C or active hepatitis B or CKnown stage IV chronic kidney disease, on dialysis at enrolment or imminent need of itParticipation in another outcome-based interventional trial within the last 30 daysPatients taking hydroxychloroquine for other indication than to treat COVID-19

Comments to the inclusion criteria: For the purpose of this study, intensive care unit is defined as a facility that allows continuous monitoring of vital functions and oxygen administration. In other cultural contexts, this could include also high dependency unit and intermediary care units or level 2 units.

It is expected that most patients will have rtPCR test known within 24 h of admission to hospital. Nonetheless, if this is not the case (e.g., due to overloaded lab facility, lack of supplies) it is possible to randomise a patient based on a strong clinical suspicion of SARS-Cov-2 infection. In the case COVID-19 is not confirmed in retrospect, experimental therapy is withdrawn, and the study subject is withdrawn from “per protocol” analysis of the primary and secondary outcomes but remains in an “intention-to-treat” cohort for the analysis of safety.

Eligibility criteria for study sites. Study sites were selected based on track-record of performing multi-centre interventional studies and willingness to participate.

### Who will take informed consent? {26a}

There is a three-step process of obtaining informed consent process compliant with Declaration of Helsinki (ver. 2008): (1) Patients with decision-making capacity will be asked by study physician to provide written prospective informed consent and consent for the use and storage of personal data as per Regulation (EU) 2016/679 General Data Protection Regulation (see Appendix). It is expected that a significant proportion of screened patients will lack the capacity to provide informed consent due to altered consciousness, respiratory distress, or sedation to facilitate mechanical ventilation. In this situation, (2) the deferred consent policy [6] will be applied in patients without capacity: patient’s legal representative will be sought to consent for the patient and if not available or approachable with reasonable effort, (3) the patient will be enrolled without consent. In the latter case, an independent physician will confirm in writing that the patient fulfils criteria and lack capacity. The patients themselves are approached to provide ongoing consent as soon as they regain capacity. They are given options to continue in the study, to withdraw with permission to use the data collected up to the point or to withdraw from the study and request deleting all data collected. This trial is fully compliant with both Declaration of Helsinki (ver. 2008) and Czech legislation. The family will be informed when practical about their relative’s enrolment into the trial based on the opinion of the independent physician and the family will be offered an information leaflet explaining the nature of the study. In the case they are of the opinion that the patient would not wish to participate in the trial, patients will be withdrawn. All serious adverse events that are suspected from being related to study interventions will be reposted to Research Ethics Board and regulatory authorities as per local legislation.

#### Item {26b}

Additional consent provisions for collection and use of participant data and biological specimens in ancillary studies, if applicable.

Additional consent provisions for collection and use of participant data and biological specimens is not applicable to our trial as no ancillary studies are planned.

## Interventions

### Explanation for the choice of comparators {6b}

At present, there is no effective drug to treat COVID-19 and hence best supportive care in addition to randomising patients into high quality RCTs is recommended by World Health Organization [7], Infectious Diseases Society of America [8], Surviving Sepsis Campaign Guidelines endorsed by European Society of Intensive Care Medicine [9], and Czech Society of Intensive Care Medicine (www.csim.cz). All patients will receive best supportive care that will be monitored, but not protocolized. It is recognised that the standard of care may substantially differ among study centres and that is why randomisation is stratified. Concomitant medication may include off label use of unproven treatments, but not participation in another outcome-based interventional trial.

Hence, the administration of a placebo in addition to best supportive care will be used in the control group.

### Intervention description {11a}

All study medication is provided as a kind gift of Zentiva, ltd. Unblinded study pharmacist will prepare 40 ml of sterile water study medication, according to patient’s allocation into the treatment arm:
Hydroxychloroquine sulphate 200 mgAzithromycin dihydrate 500 mgLactose as placebo

For possible drug-drug interactions and details of possible adverse effects, see Summary of Product Characteristics for both investigational medicinal products.

Treatment group allocation is as follows (Table 1):

**Table 1 Tab1:** Treatment allocation in 3 study arms

Study group		
HC-A (Intervention)	Azithromycin	Hydroxychloroquine
HC (ACTIVE COMPARATOR)	Lactose	Hydroxychloroquine
C (PLACEBO)	Lactose	Lactose

Each study subject will be given:
Day 1: Patients receive two doses 400 mg of hydroxychloroquine or placebo in 12 h interval and 500 mg of azithromycin or placebo once in 24 h (with the first dose of hydroxychloroquine or placebo)Days 2–5: Patients receive two doses 200 mg of hydroxychloroquine or placebo in 12 h interval 250 mg of azithromycin or placebo once in 24 h (with the first dose of hydroxychloroquine or placebo)

#### Masking

The study drugs will be administered in covered Jeannete syringe into nasogastric tube (for patients unable to swallow) or drunk from a black mug by patients who are able to. In both cases, at least 50 ml of water will be used for flushing.

### Criteria for discontinuing or modifying allocated interventions {11b}

In general, the study subject will be withdrawn from the study if any of the following criteria are fulfilled:
Consent withdrawal by study subjectIn case—in the opinion of the investigator—the study procedures are considered unsafe for the study subject or the risks outweigh the potential benefits

Specifically, for the study subjects enrolled into the study as COVID-19 suspected but without the definite result of rt-PCR testing:
If COVID-19 is negative and believed to be true negative, subjects will be immediately withdrawn from the study and administration study medication will immediately be stopped. Yet, data on adverse events will still be collected and analysed, in accordance with “intention-to-treat” mode of safety analysis

Note: In case there is a strong suspicion of COVID-19 despite negative test or if there is a doubt about the validity of the test (e.g., questionable sampling technique), it is possible and recommended to repeat the test and only withdraw the subject from the study after the confirmatory test is negative.

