### Interim analyses {21b}

We plan to perform an interim analysis after the primary outcome is known for the 120th subject. As mentioned above, primary and secondary outcomes will only be calculated in patients with confirmed COVID-19 infection who received at least one dose of IP. Adverse events will be calculated in all randomised patients (intention-to-treat analysis).

All suspected unexpected serious adverse events (SUSARs) will be reported to both REB and to the steering committee, who may decide to stop the trial for safety concerns. Apart from safety, other reasons for stopping the trial are as follows:
Emergence of new data (e.g., publication of the results of a big RCT) that may lead the continuation of the trial unethical. This may be due to safety concerns of the placebo group (in case a strong clinical benefit is proven by other trials) or any of the interventional groups (e.g., if harm is reported by other trials). This rule also applies for emergence of a new treatment.After interim analysis: The steering committee will review primary outcomes and the summary of adverse events in all 3 groups (labelled as A, B, and C) whilst still blinded to treatment allocation. The treatment can be stopped if the following criteria are fulfilled:There is a significant difference in the primary outcome at *p* < 0.017 in between the groups.Futility: The futility criterion is not binding for the steering committee. Based on available data, the study statistician calculates the probability of being able to prove the null hypothesis with achieving the target number of subjects and the probability of type II error made by stopping the trial prematurely.Safety: In case the number of adverse events in one or more treatment groups is found uneven or unacceptably high.Details of pharmacovigilance are described in a dedicated section below.

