### Methods in analysis to handle protocol non-adherence and any statistical methods to handle missing data {20c}

Primary and secondary outcomes will be calculated and reported for all patients that were found to have COVID-19 infection at enrolment and received at least one dose of study medication or placebo, whilst those who were randomised based on clinical suspicion and later found not to have COVID-19 will be excluded (per-protocol analysis). Adverse events and safety outcomes will be reported as intention-to-treat analysis. No replacement of study subjects or imputation of missing data will be made.

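### Section {11b} takes a patient out of the study, not just off study drug, on a safety judgement, while section {20c} needs that patient's outcome and allows no imputation

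*Protocol article*

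**What the plan says.** The heading of section {11b} concerns stopping or modifying the allocated intervention. The rule beneath it goes further: "In general, the study subject will be withdrawn from the study if any of the following criteria are fulfilled". Two general triggers follow. One is withdrawal of consent. The other is the investigator's opinion that "the study procedures are considered unsafe for the study subject or the risks outweigh the potential benefits".

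The section then deals with patients enrolled on suspicion whose test is a true negative. They leave the study and their study medication is stopped, which the text names as two separate acts. A further sentence adds: "Yet, data on adverse events will still be collected and analysed, in accordance with “intention-to-treat” mode of safety analysis". No such sentence follows the safety trigger.

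Section {20c} defines the efficacy analysis. Primary and secondary outcomes are "calculated and reported for all patients that were found to have COVID-19 infection at enrolment and received at least one dose of study medication"; a dose of placebo counts equally. The only exclusion it names is patients later found not to have COVID-19. It adds: "No replacement of study subjects or imputation of missing data will be made". For safety it says: "Adverse events and safety outcomes will be reported as intention-to-treat analysis". The section on interim analyses {21b} likewise counts adverse events in everyone randomised.

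**The concern.** A dosed patient with confirmed COVID-19 whose investigator stops treatment for safety is in the analysis set under {20c} and out of the study under {11b}. A site that follows {11b} to the letter could stop collecting that patient's data. Status at days 14, 28 and 90 could then be missing, and with no imputation the patient drops out of the primary chi-square comparison.

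This loss need not be random. The Discussion names QT prolongation, life-threatening arrhythmia and retinopathy as possible harms of the study drugs, so safety stops may be more frequent in an active arm and may be related to prognosis. If the lost patients would have done worse than average, the active arm looks better than it is; if better, it looks worse. Later adverse events in the same patients could be missing in the same unequal way, and they are the patients in whom those events matter most.

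**Working it through.** **1. The texts side by side**

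| Patient | Action in {11b} | Collection after withdrawal, as written in {11b} | Required by the analysis sections |
|---|---|---|---|
| Randomised on suspicion, later negative | Leaves study and drug stopped | Adverse events | Adverse events only |
| COVID-19 positive, dosed, stopped for safety | Leaves study | Nothing stated | Primary and secondary outcomes, and adverse events |
| Consent withdrawn | Leaves study | Nothing stated; {26a} gives the patient's options, including use of data up to withdrawal or deletion | Whatever the patient permits |

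Two features of {11b} support the literal reading of the second row. First, it treats leaving the study and stopping the drug as different acts. Second, the adverse-event sentence for negative patients opens with a contrasting word, so continued collection is presented as an exception to what withdrawal would otherwise mean. Section {11c} covers only temporary omission of doses with reloading. No section provides a permanent stop of study drug alone.

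**2. Timing**

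Dosing covers days 1 to 5 (section {11a}) and the primary outcome is recorded at day 14 (section {13}). A stop during dosing therefore comes at least 14 − 5 = 9 days before the endpoint.

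**3. The plan's own sample size**

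Inputs from section {14}: 25% against 50%, p < 0.017, 80% power, 74 per arm, 240 enrolled. Two-sided testing is assumed.

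- Unpooled formula: n = (z for two-sided 0.017 + z for 80% power)² × (0.25 × 0.75 + 0.50 × 0.50) / 0.25² = 72.95, so 73 per arm. The stated 74 is reproduced to within one patient; power at 74 per arm, with pooled variance, is 0.783.
- Drop-out allowance: 240/3 − 74 = 80 − 74 = 6 per arm, which is 6/80 = 7.5%, or 18 in total.

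**4. Size of a possible bias**

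The documents give no rate of safety withdrawal, so the following is an illustration. Assumptions: 80 patients per arm, all dosed and positive; a true success rate of 25% (20/80) in both arms; k safety withdrawals with missing day-14 status in one active arm and none in control. Let s be the number of successes among the k.

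Observed active rate = (20 − s) / (80 − k)

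| k (share of arm) | All would have failed (s = 0) | Typical (25% succeed) | All would have succeeded (s = k) |
|---|---|---|---|
| 4 (5%) | 20/76 = 26.3% | 19/76 = 25.0% | 16/76 = 21.1% |
| 6 (7.5%) | 20/74 = 27.0% | 25.0% | 14/74 = 18.9% |
| 8 (10%) | 20/72 = 27.8% | 18/72 = 25.0% | 12/72 = 16.7% |

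Against the true 25%, the bias is +1.3 to +2.8 points in the first case, zero in the second, and −3.9 to −8.3 points in the third.

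**5. False-positive risk when all the lost patients would have failed**

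Exact enumeration of the uncorrected chi-square test at two-sided 0.017, with control Bin(80, 0.25) and active Bin(80 − k, 20/(80 − k)), gives this chance of a false result favouring the drug:

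| k | 0 | 4 | 6 | 8 |
|---|---|---|---|---|
| Chance | 0.87% | 1.43% | 1.79% | 2.39% |

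**The case against.** The strongest reply is that the article contains ambiguity rather than contradiction. Section {20c} defines who is analysed and {11b} defines an action; they collide only if withdrawal ends data collection, and no section says that it does. Patients who test negative leave the study and still supply data, so in this document withdrawal does not by itself mean that collection stops. Such a patient leaves the per-protocol efficacy analysis "but remains in an “intention-to-treat” cohort for the analysis of safety", and the safety analysis covers everyone randomised. Section {13} schedules days 14, 28 and 90 without exception, and {18b} regards vital and ventilation status as easy to obtain by telephone. A full protocol exists and may say more. The illustrated bias is also small in a trial designed for a 25-point difference, and the adverse case stacks several assumptions.

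Much of this stands. The intent was probably to keep following these patients, the withdrawal rate is unknown, and typical patients would cause no bias. What does not stand is treating the point as mere silence. The article states a rule, that rule is removal from the study, and it groups a safety stop with withdrawal of consent. Negative patients are a poor precedent, because they are outside the efficacy analysis and only their adverse events are needed. Blinding of site investigators does not prevent imbalance either, since real toxicity can produce unequal stops. An analysis plan cannot recover a day-14 status that a site never recorded.

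**Conclusion.** The concern holds. Read literally, {11b} takes out of the study patients whom {20c} requires in the outcome analyses, and it secures adverse-event follow-up only for patients without COVID-19. The rest of the article suggests that this was not intended, so the defect is a stated rule that does not match the plan's own aims.

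The size is unknown but probably modest. With an assumed 5% to 10% of one active arm lost and none in control, the apparent success rate moves by between +2.8 and −8.3 points depending on who is lost, and not at all if they are typical. If all of them would have failed, the chance of a false result favouring the drug rises from 0.9% to at most 2.4%. The correction should be made because the loss is avoidable, may differ between arms, and costs almost nothing to prevent.

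**What to change.** Change two sentences in {11b}:

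1. State that an investigator's safety concern stops study drug only. The subject stays in follow-up for adverse events and for the existing daily, day-14, day-28 and day-90 contacts unless consent is withdrawn, in which case the options in {26a} apply.
2. Extend the sentence on continued adverse-event collection to everyone who stops study drug without withdrawing consent.

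The criteria that trigger a stop, the analysis sets and the sample size stay as they are. The cost is completing visits or calls that are already planned for a few patients.
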